## Abstract

**Background:**

Conducting high-quality randomized clinical trials (RCTs) is challenging, time consuming, and resource intense. Academic investigators usually depend on scarce financial resources; however, current literature lacks systematically collected empirical data on the detailed resource use and costs of investigator-initiated RCTs.

**Methods:**

The aim of this study is to generate a database of detailed empirical resource use and cost data from 100 investigator-initiated RCTs in Switzerland, Germany, and the UK. Investigators enter their empirical costs data into an online data collection form, which is followed by a short interview and a detailed cost report. We plan to investigate cost patterns and cost drivers and examine planned versus actual RCT costs as well as explore different strata of costs across the planning, conduct, and finalization phases, in drug and non-drug trials, and across medical fields and countries.

**Discussion:**

This study will add detailed empirical data to the limited research on investigator-initiated RCT costs currently available. A study limitation will be that cost data will be retrospective and self-reported, which might be inaccurate depending on how costs were recorded.

**Trial registration:**

Open Science Framework (OSF) https://doi.org/10.17605/OSF.IO/QY2GU. Registered on June 4, 2021.

**Supplementary Information:**

The online version contains supplementary material available at 10.1186/s13063-024-08505-y.

## Background

Randomized clinical trials (RCTs) are the cornerstone of reliable evaluation of interventions in health care, with results that often impact clinical guidelines and evidence-based practice ultimately leading to better health care for patients [1–3]. However, conducting high-quality RCTs is challenging, resource intense, and associated with high costs [4, 5]. Tens of billions of dollars of public and private money are invested in RCTs every year, estimated to reach $68.9 billion a year by 2025 [6]. Moreover, RCT costs are rising. Over the last decade, a number of new initiatives and regulations were implemented to increase participant protection and to improve research quality [2, 7–10]. As a consequence, the complexity and administrative burden of RCTs have increased overall costs [11–15]. Furthermore, the implementation of medical advances, while highly desirable, has limited the incremental impact of new therapies, resulting in smaller beneficial effects of interventions, which requires larger RCT sample sizes [16, 17]. All these developments have resulted in escalating RCT costs, thus exasperating the problem of scarce resources for academic clinical research.

One consequence of these cost pressures is that the number of independent investigator-initiated RCTs has remained constrained over the last two decades [2, 18, 19] and a substantial proportion of these trials are prematurely discontinued due to recruitment and organizational problems [19], which risks many clinical research questions remaining unaddressed. Therefore, efforts to make investigator-initiated RCTs more cost-effective and sufficiently funded are urgently needed.

In spite of this, the literature on how much RCTs actually cost remains sparse [20–22]. It was only in the last few years that the first systematic investigations addressing RCT costs have been published [20, 21, 23]. Sertkaya et al. analyzed aggregated cost data of clinical trials sponsored by the pharmaceutical industry in the USA between 2004 and 2012 and reported average costs of phase III trials ranging from US$ 11.5 million (dermatology) to US$ 52.9 million (pain and anesthesia) and of phase II trials ranging from US$ 7.0 million (cardiovascular) to US$ 19.6 million (hematology) [23]. Apart from trial phase, the authors identified therapeutic area as well as the number and types of clinical procedures involved as key drivers of direct costs in pharmaceutical RCTs. Another study collected cost data directly from seven major biopharma companies including 726 interventional studies conducted from 2010 to 2015 using a standardized approach to assign clinical development spending to individual trials [21]. The median trial costs from protocol approval to the final report proved to be US$ 21.4 million for phase III trials and US$ 8.6 million for phase II trials with huge variability around these averages (e.g., 25th and 75th percentile for phase III trials of US$ 9 million and US$ 44 million, respectively). The authors derived a multivariable model including number of trial sites, therapeutic area, and treatment duration as main independent variables that explained 60–90% of the variance of overall trial costs in phase II and phase III trials. Finally, Raftery et al. reported the analysis of metadata on 125 published RCTs funded by the National Institute for Health Research Health Technology Assessment programme (UK) between 1995 and 2005, including cost data [20]. The authors calculated mean total trial costs ranging between £0.5 million and £2.4 million. They further showed that the actual costs exceeded the planned costs in 78% of projects, with 57% of projects exceeding by 10% or more and 12% exceeding by 50% or more. In multivariable regression analyses, they identified a greater number of trial sites and longer trial duration as the independent variables associated with higher trial costs, explaining 40% of the variance in their model.

None of these three studies provided a detailed breakdown and relative weights of specific cost items, nor did they provide associated resource use data (e.g., hours of trial staff time used), both of which would be required for insights into potential efficiency gains [24]. Those sort of insights have only been derived from simulation studies investigating strategies to reduce RCT costs [12, 25] and the intuition of experienced trial leaders [2, 14]; both of which have repeatedly criticized extensive on-site monitoring as a major cause for increasing costs of RCTs and suggested more streamlined approaches. Site monitoring with source data verification was estimated to account for 15–30% of clinical trial costs in industry sponsored trials [12, 23, 25, 26]. Respective estimates for monitoring costs from investigator-initiated RCTs are, except for a recent case report by our group [27], not available. In a systematic review of studies reporting empirical data on resource use and costs of RCTs up to November 2016 by our group [22], we identified 56 articles that provided some information on resource use or costs in RCTs, but no study comprehensively presenting detailed resource use and associated costs for the entire course of an RCT. A more recent study used activity-based costing methodology to assess the estimated total costs of nine randomized phase 3 clinical trials with new anticancer biological agents [28]. Nevertheless, the current empirical evidence on the topic lacks comprehensiveness, transparency, detail, and a standardized methodology to assess consumed resources and costs. As a consequence, the usefulness of the available data for clinical researchers, academic institutions, biomedical companies, regulators, or funding agencies remains extremely limited.

In collaboration with several stakeholders, we developed a comprehensive costing list, with which we collected detailed data from two investigator-initiated RCTs to exemplify how costs and resource use can be systematically assessed and presented [27]. The final list comprised of fixed costs and variable costs built upon a list of study activities (activity-based costing) [29–31]. In both trials, personnel costs during patient enrolment, treatment, and follow-up accounted for the majority of expenditures. Data monitoring costs in both investigator-initiated RCTs, including source data verification, accounted for less than 1% of total costs, in contrast with 10–30% for industry trials [12, 23, 26]. Generalizing beyond these two trials, however, requires a large systematic investigation on cost structures and cost drivers in RCTs. Therefore, we aim in the present protocol to empirically investigate detailed resource use and cost data from a large sample of investigator-initiated RCTs in three countries.

## Study objectives and hypotheses

The aim of this study is to generate a database of detailed empirical resource use and cost data from 100 investigator-initiated RCTs in Switzerland, Germany, and the UK, so that we can descriptively investigate total RCT costs and proportions of total costs for individual cost items to achieve the following specific objectives:A)To investigate cost patterns on an absolute (actual costs in USD) and relative scale (% of total costs) including largest cost items for the whole RCT and for the planning, conduct, and finalization phases.B)To explore RCT costs across different strata including medical fields, intervention types, multicenter/single center status, and countries.C)To examine planned versus actual RCT costs and to explore factors that explain excess costs.D)To explore hidden costs associated with conducting an RCT such as resource use and costs for writing the protocol, trial committees, ongoing communication, and managing serious adverse events (SAEs).

We have the following specific hypotheses:(i)The expenses for participant recruitment and follow-up typically constitute the largest proportion of total RCT costs.(ii)Data monitoring constitutes—on average—less than 15% of total RCT costs.(iii)Delays in recruitment of trial participants explains most of the excess costs.(iv)Cost structures (proportions) and fixed cost items (e.g., regulatory or ethics committee approval) are similar across medical fields and countries.

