### Study design

This is an observational study for which we aim to retrospectively collect detailed empirical cost and resource use data from 100 investigator-initiated RCTs from three different countries (Switzerland *n* = 60, Germany *n* = 20, UK *n* = 20). This study was registered on Open Science Framework [32]. This study does not collect any patient- or health-related data and does not require ethical approval (confirmed by EKNZ Project ID: Req-2024–00581).

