### Data collection procedures

Protocols and publications will be collected for each of the RCTs and the cost data will be collected and stored in the electronic data capture system REDCap [33, 34]. Trial teams will enter their cost and resource data directly into an online data collection form. Data entry will be followed by a short interview to clarify unclear values and missing data. A cost report will be generated for each trial, which is then reviewed by the trial team. Funders of RCTs were not contacted, since previous research has shown that budgets are purposefully underestimated and we wanted to record the actual costs of RCTs [35].

For the collection of the resource use and cost data, we will use a previously developed and tested cost item list developed by Speich et al. that follows principles of activity-based costing [27, 36]. An overview of the collected variables can be found in Table 1. All variables and the online data collection form can be found in the supplementary material (Supplement Table 1 and Supplement Table 2). The online cost report form will be tested on two RCTs and changes will be made based on the feedback provided by investigators and study teams.

**Table 1 Tab1:** Total trial costs

**Total Trial Costs ** • Trial Budget • Trial Funding • Total trial costs • Total trial costs adjusted for employer contributions • Total trial costs adjusted for employer contributions and 30% unaccounted time • Total trial costs adjusted for employer contributions, 30% unaccounted time and overhead		
**Planning**	**Conduct**	**Finalization**
**Fixed Costs** • Ethics Committee approval fees • Health authority fees • Other approval fees • Costs for Infrastructure and Equipment • Shipping costs • Insurance fees	**Fixed Costs** • Advertisment • Costs of Intervention • Placebo manufacturing • Additional procedures and material • Patient reimbursement • Specimen analysis • AE/SAE/SUSAR material • Travel costs • Audits and Inspections	**Fixed Costs** • Publication fees • Conference fees and costs

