We will calculate excess costs for each RCT (delta of originally planned total costs and actual total costs [Total costs − Planned Costs]). This will help investigate trial characteristics associated with excess costs of an RCT (dependent variable). We will develop a multivariable regression model with delta in recruitment duration, actual sample size, and actual number of trial sites, country, intervention type, and medical field as independent variables (objective C).

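### The regression planned for excess costs cannot show whether recruitment delay accounts for most of the excess, which is what hypothesis (iii) claims

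*Protocol article*

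**What the plan says.** All references are to the protocol article.

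- **Study objectives and hypotheses.** Objective C is exploratory: "To examine planned versus actual RCT costs and to explore factors that explain excess costs". Among the specific hypotheses, (iii) makes a majority claim: "Delays in recruitment of trial participants explains most of the excess costs". No measure of 'most' is given.
- **Study design.** "This is an observational study for which we aim to retrospectively collect detailed empirical cost and resource use data".
- **Statistical analysis, excess-cost model.** The outcome is the "delta of originally planned total costs and actual total costs", written out as total minus planned costs, so it is an absolute amount of money. The regressors are "delta in recruitment duration, actual sample size, and actual number of trial sites, country, intervention type, and medical field as independent variables". The model is introduced with "This will help investigate trial characteristics associated with excess costs of an RCT (dependent variable").
- **Statistical analysis, descriptive part.** Reasons that investigators report for missing the budget, and for prolonged recruitment, are put into categories. Planned and actual cost, recruitment duration and sample size are compared for each trial. Summaries are stratified by over- or under-budget status at ±10%.
- **Data collection procedures.** Funders were not approached because "previous research has shown that budgets are purposefully underestimated and we wanted to record the actual costs of RCTs".

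**The concern.** A claim that delay accounts for most of the excess concerns a fraction: excess dollars tied to delay, divided by all excess dollars. The planned model returns a coefficient, the difference in excess per unit of recruitment delta with other characteristics held fixed. Neither its size nor its p-value says whether the fraction exceeds one half.

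The gap matters because the article itself describes another source of excess. Planned cost is subtracted in the outcome, so every dollar by which a budget is set too low adds a dollar of excess, with or without delay. No regressor represents this. The descriptive analyses can reveal it as a category of reason or a pattern, but not as a share of the excess.

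At stake is the message of objective C. Funders and investigators could be told that slow recruitment is the main source of overruns when most of the excess would have arisen without any delay.

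**Working it through.** The article gives no figure for (iii) to reproduce. The check compares the hypothesis with the model and then uses an illustration whose inputs are all assumed.

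**1. Two different quantities.**
- Hypothesis: share = (sum of excess associated with delay) / (sum of excess).
- Model: the coefficient of the recruitment delta, given sample size, number of sites, country, intervention type and medical field.

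The second gives the first only after it is multiplied by the deltas, summed and divided by total excess. The article does not state that step.

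**2. Share under an assumed shortfall.** Let every budget be too low by a fraction s, and let delay add 10% of budget on average. Then share = 0.10 / (s + 0.10).
- s = 0.30: 0.10/0.40 = 25%
- s = 0.20: 0.10/0.30 = 33%
- s = 0.10: 0.10/0.20 = 50%

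**3. What the regression would show in the 25% case.** Assumptions: 80 trials with a usable budget; s = 0.30; delay cost gamma-distributed with mean and SD 10% of budget; residual SD 5% of budget; excess in dollars, as the article defines it; budgets lognormal, with the coefficient of variation (CV) shown. The model contains delay and a noisy proxy for trial size. With equal budgets a size proxy carries no information.

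| Budget CV | Partial R² of delay | Runs with delay p<0.05 | True share |
|---|---|---|---|
| 0 (all equal) | 0.79 | 100% | 25% |
| 0.5 | 0.27 | 99% | 25% |
| 1.0 | 0.15 | 88% | 25% |
| 1.5 | 0.11 | 70% | 25% |

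A repeat with a log-scale error SD of 0.5 in the size proxy agreed to within 0.01 in partial R² and 3 percentage points in significance. With delay as the only regressor, R² at CV 0.5, 1.0 and 1.5 was 0.19, 0.07 and 0.05, and delay was significant in 95%, 54% and 32% of runs.

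So significance says little about the share. It is frequent in most of these settings although delay never accounts for more than a quarter of the excess.

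**4. How well the share can be estimated.** At CV 1.0 with the size proxy, the estimate of (delay coefficient × delta, summed) / (summed excess) ran from about 0.08 to 0.49 across simulated studies, around the true 0.25. With delay alone it ran from 0.01 to 0.57. The share is recovered on average, but imprecisely.

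**5. Why excess at zero delay is not the budget shortfall alone.** Under Data management, actual variable costs are raised by 30% for unaccounted time. Suppose a planned budget lacks that uplift and variable costs are 50% to 90% of the total (both assumed). The uplift alone then gives 0.30 × 0.50 = 15% to 0.30 × 0.90 = 27% apparent excess. Other causes can add to this.

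**The case against.** The strongest reply has four parts.

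- **Objective C is exploratory.** The model is described in terms of association, and no decision rule for (iii) is stated. This stands: a reader might infer that the investigators will take a significant delay coefficient as confirmation, but the article does not say so. Even so, (iii) is listed as a specific hypothesis with a majority claim, and the stated model cannot answer it on any reading of its coefficient.
- **Under-budgeting is not absent from the study.** Categorised reasons and the planned-versus-actual comparisons would show an overrun in a trial that recruited on time. This also stands. A reader might infer that the plan overlooks a rival cause that it has itself named. In fact the remark "previous research has shown that budgets are purposefully underestimated" is offered as a reason for not contacting funders. Its link to excess follows from the definition of the outcome, not from a statement in the article. What the descriptive analyses do not give is a share.
- **A common shortfall need not hide in the intercept.** A reader might infer that delay could explain about 80% of the variance yet only 25% of the dollars. That contrast holds only if all budgets are equal or excess is expressed as a percentage of budget. The outcome is in dollars, so a proportional shortfall grows with trial size and lowers the R² of delay, as the table shows.
- **The delay coefficient may be unbiased.** A reader might infer that omitting budget realism inflates it. That would require underestimation to be correlated with delay, and the article gives no information on this.

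It is also fair to say that a share built from the same coefficient remains an association with a wide interval. That limits how its result may be worded. It does not make the coefficient alone an answer to (iii).

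**Conclusion.** The point holds as a mismatch between a hypothesis and its stated analysis. Hypothesis (iii) concerns a majority of excess cost, while the planned regression yields an adjusted association that cannot show a majority. In the assumed example, delay carries 25% of the excess and its coefficient is significant in 70% to 99% of runs when budgets vary and a size proxy is in the model. These figures depend on the assumed shortfall, delay cost, residual spread, budget spread and 80 usable trials, none of which the article gives. They show that the misleading pattern can occur, not how often it will. The finding does not rest on a high R², on bias in the delay coefficient, or on the article having declared how it will judge (iii). It merits a change to the analysis of objective C and leaves the rest of the design untouched.

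**What to change.** For hypothesis (iii):

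1. Report the model-based share of summed excess associated with delay: the sum of (delay coefficient × recruitment delta) over the sum of excess, with a bootstrap 95% CI.
2. Report beside it the observed excess in trials that recruited on time, in dollars and as a percentage of planned cost, and the model-predicted excess at zero delay. Describe the latter as excess from all causes other than delay, not as the budget shortfall.
3. State how under-budget trials and negative recruitment deltas are handled, since both enter the sums with the opposite sign.
4. Word the conclusion as an association, and do not take a significant delay coefficient or an R² as support for 'most'.

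The cost is some wording and a few lines of code. Planned and actual recruitment duration and, where available, originally planned costs are already on the extraction list. The downside is precision: the interval is likely to be wide, and (iii) may have to be reported as inconclusive.

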### Study design

This is an observational study for which we aim to retrospectively collect detailed empirical cost and resource use data from 100 investigator-initiated RCTs from three different countries (Switzerland *n* = 60, Germany *n* = 20, UK *n* = 20). This study was registered on Open Science Framework [32]. This study does not collect any patient- or health-related data and does not require ethical approval (confirmed by EKNZ Project ID: Req-2024–00581).

### Eligibility criteria and trial identification

RCTs will be included if they have been completed or are close to completion (statistical analysis ongoing or manuscript in preparation). Trials will be excluded if they are industry sponsored, dose-finding RCTs, RCTs primarily evaluating pharmacokinetics or physiology, include healthy volunteers, or RCTs that published results more than 10 years prior to the start of this investigation. To enhance comparability across countries, we will aim to include 10–15 RCTs each from cardiovascular, oncology, surgical, and miscellaneous fields. However, it was challenging to find principal investigators willing to share their cost data, as such we decided to expand our scope and include a small sample of pilot studies (*n* = 10) and RCTs initiated in Switzerland but conducted in low- and lower-middle-income countries (*n* = 10).

We will identify potentially eligible RCTs using two approaches: Firstly, we will use a convenience sample and contact Clinical Trial Units (CTUs), trial networks, and individual principal investigators known to the authors in all three countries and ask them about eligible investigator-initiated RCTs they could contribute. Most of our direct trialist connections are in Switzerland. In particular, we will approach the Swiss CTU network; the KKS Network, UK Registered CTUs Network; Network of Hubs for Trials Methodology Research (UK); UK Trial Managers’ Network, Trial Forge Initiative (UK); Koordinierungszentren für Klinische Studien Network (DE); Oncology network (DE); and the Clinical Trials Centre Cologne (DE).

Secondly, we will screen trial registries for completed RCTs and then invite principal investigators to participate in our study. These trial registries will include clinictrials.gov, the ISRCTN registry, the Health Research Authority (NHS) registry, Kofam (Swiss Clinical trial registry), and the Deutsches Register Klinischer Studien (DRKS; the German clinical trial registry).

For each RCT contributed to the project, we will offer the trial teams 200 euros as a compensation for their efforts.

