### Sample size considerations

We simulated data sets with various numbers of RCTs to study how many RCTs we would need to achieve a 90% probability (statistical power) for a sufficiently narrow 95% confidence interval (CI) around the estimated mean cost proportions for individual cost items. We assumed that a 95% CI width of 6% (i.e., a maximum of ± 3%) for the estimated mean would be sufficiently precise. The confidence interval assumes a normal distribution and is calculated as 1.96 * the standard error. Figure 1 shows how the required sample size depends on the true average proportion. Note that there are two lines: a dark line for a rather wide assumed distribution of proportions (tau = 10; beta distribution with a precision of 10) and a gray line for a plausible, narrower distribution (tau = 20). According to the dark line (the wider distribution), including a total of 60 RCTs would suffice to achieve a power of 90% to find a satisfyingly narrow 95% CI of 6% for a mean proportion below 0.15. Thus, our original plan was to include at least a total of 180 RCTs which appeared appropriate to achieve sufficient precision for estimated proportions (even within subgroups such as countries). However, it proved extremely challenging to find principal investigators willing to share detailed resource use and cost data of their trials rendering the target sample size of 180 RCTs unfeasible. Therefore, we reduced our target to 100 RCTs (Switzerland *n* = 60; Germany *n* = 20; UK *n* = 20). This number is feasible and will still allow for sufficient precision of unstratified estimates and to conduct multivariable regression analyses without overfitting models.

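### The aim of 10–15 RCTs per medical field does not fit the 60/20/20 target on either reading, which leaves the descriptive country comparison of cost shares without protection against differing field mix

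*Protocol article*

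**What the plan says.** The section on eligibility criteria and trial identification states the aim and its purpose together: "To enhance comparability across countries, we will aim to include 10–15 RCTs each from cardiovascular, oncology, surgical, and miscellaneous fields". It does not say whether the 10–15 applies within each country or over the whole sample. The following text reports difficulty in finding willing investigators and adds pilot trials and trials in low- and lower-middle-income countries, but leaves the field figure as it is.

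The study design section sets the total: "detailed empirical cost and resource use data from 100 investigator-initiated RCTs from three different countries". The sample size section explains how it was reached. It records that "our original plan was to include at least a total of 180 RCTs", a number thought adequate for precision "even within subgroups such as countries". It then says "Therefore, we reduced our target to 100 RCTs", split as "Switzerland *n* = 60; Germany *n* = 20; UK *n* = 20", and now claims sufficient precision only for unstratified estimates.

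Country contrasts remain in the plan. Objective B explores costs across strata that include medical field and country. Hypothesis (iv) expects cost proportions and fixed cost items to be similar across both. The statistical analysis section puts field and country together in the regressions for total cost, cost per patient and excess cost. For cost proportions by stratum it describes summaries and plots by field, intervention type and country.

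**The concern.** The 10–15 per field is the only design feature in the article that is meant to align medical field across countries. If it cannot be met, the field mix in each country depends on who agrees to take part.

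Two points in the article make this more than theoretical:

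- The Background section reports therapeutic area as a driver of trial costs. In one industry analysis, average phase III costs ran from US$ 11.5 million to US$ 52.9 million by area. These are total costs rather than shares, but they show that field matters.
- Recruitment rests partly on a convenience sample. The named sources include an oncology network in Germany and no field-specific network in the other two countries.

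At stake is the reading of hypothesis (iv). A crude country difference in a cost share, or an apparent similarity, could partly reflect different field mixes. A reader told that the quota serves comparability would assume that field had been balanced.

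**Working it through.** **Inputs.** Four fields at 10–15 RCTs each (eligibility section). Target 100, split 60/20/20 (study design and sample size sections). Collected so far: 87, of which Switzerland 43, Germany 20, UK 16, and low- and lower-middle-income countries 8 (study status).

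**Reading 1: per country.**
- Needed per country: 4 × 10 = 40 to 4 × 15 = 60.
- Needed in all: 3 × 40 = 120 to 3 × 60 = 180. Even the lower end exceeds 100.
- Switzerland: 60 available, so the aim can be met (60/4 = 15 per field).
- Germany and the UK: 20 each against at least 40. The average is 20/4 = 5 per field, and at most 20/10 = 2 of the four fields could reach 10.

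**Reading 2: pooled over countries.**
- Needed in all: 40 to 60. If the miscellaneous field takes everything not in the other three, 100 RCTs exceed the upper end by 40 and average 100/4 = 25 per field. The 87 already collected exceed it by 27.
- If 10–15 is only a floor, it is compatible with 100. A pooled floor still does not align countries: all the trials in one field could come from Switzerland and the floor would be met.

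**Chance imbalance without a working quota (assumption: each field has a 25% share).** For Binomial(20, 0.25), P(X ≤ 2) = 0.091 and P(X ≤ 3) = 0.225. A country of 20 therefore has about a 9% chance of two or fewer RCTs in a given field, and about 23% of three or fewer.

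**Possible effect on a crude country contrast (assumed illustration, no source in the documents).** If an item's mean share differs by 10 points between two fields, and the mix of those fields differs by 30 percentage points between countries, the crude means differ by 10 × 0.30 = 3 points. Halving the field gap gives 1.5 points. Cutting the mix gap to a third gives 1 point. Doing both gives 0.5 points.

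**Sampling noise for comparison (the plan's wider distribution, tau = 10, mean share 0.10).** SD = √(0.10 × 0.90/11) = 0.0905. The 95% half-width is 1.96 × 0.0905/√20 = 0.040 for a country of 20, and 0.023 for 60. For a 20-versus-60 difference it is √(0.040² + 0.023²) = 0.046, or about 4.6 points.

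**Places still open.** 100 − 87 = 13. Germany has 20 − 20 = 0 and the UK 20 − 16 = 4. The other 9 are Swiss if the 8 trials in low- and lower-middle-income countries count towards the Swiss 60 (60 − 43 − 8 = 9), which the article does not state.

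**The case against.** The strongest case on the other side has five parts.

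- **The wording is an aim and is ambiguous.** It does not say per country, and a pooled floor would not contradict 100. This stands as far as it goes, so there is no flat contradiction on every reading. But the stated purpose is comparability across countries, and no pooled reading serves it.
- **The models already adjust for field.** This stands for total cost, cost per patient and excess cost. A reader might infer that all country contrasts are exposed to field imbalance; the article does not support that. None of the stated models has cost proportions as its outcome, however, and those are what the first half of hypothesis (iv) concerns.
- **The comparisons are exploratory.** Objective B explores, no formal test of hypothesis (iv) is stated, precision is claimed only for unstratified estimates, and the Discussion concedes selection. The article also says that cost proportions will first be plotted, so further steps may sit in a document not shown. This limits the weight of the point. It does not repair the quota.
- **The size of any bias is unknown.** This stands. The 3-point figure is one assumed scenario and is smaller than the 4.6-point noise of a 20-versus-60 contrast. A reader might set it against the ±3% precision target, but that target is for the unstratified mean.
- **Recruitment is nearly finished.** This stands. No new quota can change Germany.

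A reader might also infer that the quota is a remnant of the 180-trial plan, because 3 × 4 × 15 = 180. The article does not say so. It links 180 to precision of cost proportions, and the lower end of the range gives 120. The misfit does not depend on where the figure came from.

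**Conclusion.** The point holds in limited form. The field aim does not deliver its stated purpose under the current target: per country, Germany and the UK have 20 RCTs each where 40–60 are needed; as a pooled range it gives 40–60 against 100 and does not balance field between countries. The pooled mismatch assumes that the four fields are exhaustive and that 15 is an upper limit. The failure to align countries needs neither assumption.

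The consequence is confined to the descriptive country comparison of cost proportions. Its size cannot be determined from the article. This is worth correcting because the text promises a comparability that the numbers cannot provide. It does not undermine the unstratified estimates or the regressions as specified.

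**What to change.** 1. In the eligibility section, state whether the field figure is pooled or per country, and restate it to fit 100 RCTs. For example, averages of about 5 per field in Germany and the UK and 15 in Switzerland give 4 × 5 + 4 × 5 + 4 × 15 = 100. Alternatively, withdraw the claim that the quota secures comparability across countries.
2. Use the restated figure only to guide the roughly 13 places still open. It cannot alter Germany, and the UK has 4 places left.
3. Report the field-by-country count table.
4. For the main cost shares, show country contrasts adjusted for field (by regression or standardisation, merging sparse cells) beside the crude ones, labelled exploratory.

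The cost is a sentence or two of text, one table and one extra set of summaries; no collected data change. The downside is wider intervals for the adjusted contrasts. With about 5 RCTs per cell on average in Germany and the UK, and fewer in some cells, equal-weight standardisation could be unstable unless cells are merged. Steering the last invitations by field may also be hard, given the recruitment difficulty the article describes.
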